#### Secondary aims

To determine the effect of family-administered delirium prevention, detection, and management in critically ill patients on family member symptoms of psychological distress, compared to usual care.To determine the effect of family-administered delirium prevention, detection, and management on the prevalence (ever/never delirium as indicated by an Intensive Care Unit Delirium Screening Checklist [ICDSC] score ≥ 4), duration (total days of an ICDSC score ≥ 4), and severity of delirium (as indicated by the ICDSC score, which ranges from 0 to 8) in critically ill patients, compared to usual care.To determine the effect of family-administered delirium prevention, detection, and management on the diagnosis of the patient with delirium (ICDSC score ≥ 4), compared to usual care.To determine the effect of family-administered delirium prevention, detection, and management on family member knowledge of delirium in critically ill patients, compared to usual care.To determine the effect of family-administered delirium prevention, detection, and management on the burden of delirium (e.g., feelings of helplessness) experienced by family members of critically ill patients, compared to usual care.

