### Eligibility criteria

Consecutive, eligible (Table 1) patients with at least one family member (defined here as family, relatives, or friends) present in the ICU will be approached by a patient advisor or research assistant to participate (Additional file 1). The patient and family member will be enrolled in the study as a dyad. Participants will be recruited at any point during their ICU admission, and participation will occur to a maximum of 5 days, or until ICU discharge or death. Anticipated study flow is presented in Table 2. If more than one family member is present, the study team will enroll the family member most familiar with the patient or the familiar expected to visit the most (and provide complete data).

**Table 1 Tab1:** Study Inclusion and Exclusion Criteria

	Dyad	
	*Patient*	*Family*
Inclusion Criteria	• Age 18 years of age or above	• Age 18 years of age or above
	• Family member present	• Present
	• Richmond Agitation Sedation Scale score ≥ −3 (eligible for delirium assessment)	
Exclusion Criteria	• Unable to provide informed consent (patient or family member)	• Unable to provide informed consent (patient or family member)
	• Inability to communicate with the research staff (e.g., no hearing impairment and must be fluent in English)	• Inability to communicate with the research staff (e.g., no hearing impairment and must be fluent in English)
	• Anticipated to remain in ICU for less 24 h	• Anticipated to remain in ICU for less 24 h
	• Primary neurological injury (e.g., severe traumatic brain injury, subarachnoid hemorrhage)	
	• Glasgow Coma Scale score < 9

**Table 2 Tab2:** Schedule of enrolment, interventions, and assessments

Activity / assessment	CRF (Yes/No)	Staff Member	-1 Prescreening / consent	0 Baseline / Randomization	T1 Immediately post-randomization	T2 Daily for Remainder of ICU stay	F1 Follow-up 1-month	F2 Follow-up 3-months
Prescreening consent	No	Nurse unaffiliated with study	X					
Screening log	No	Research Assistant	X					
Consent form	No	Research Assistant	X					
Inclusion/Exclusion form	Yes	Research Assistant	X					
Randomization	No	Biostatistician unaffiliated with study		X				
Patient demographics form	Yes	Research Assistant		X				
Family member demographics form	Yes	Research Assistant		X				
Educational video/booklet	No	Research Assistant			X			
Delirium prevention and management	Yes	Research Assistant				X		
Delirium detection (Sour Seven)	Yes	Research Assistant				X		
CIDKQ	Yes	Research Assistant		X		X	X	X

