For the primary aim, we will report a difference in proportion of the clinically significant symptoms of depression [PHQ-9] and anxiety [GAD-7], mean PHQ-9 and GAD-7 scores, and frequency of categories of depression and anxiety (i.e., minimal, mild, moderate and severe) (at discharge from ICU, 1-, and 3- month follow-up) between control and intervention groups. For secondary aims we will report: 1) A difference in proportion of the most severe family members symptoms of psychological distress [K-10] (at discharge from ICU, 1-, and 3- month follow-up) between control and intervention groups. 2) Prevalence of delirium: Difference in proportion of patients with clinical delirium (ICDSC score ≥ 4) pre-post intervention (in-ICU) between control and intervention groups. Duration of delirium: Difference in mean days with clinical delirium (ICDSC score ≥ 4) pre-post intervention between control and intervention groups (in-ICU). Duration of delirium-free days: Difference in mean days without delirium on the ICDSC pre-post intervention between control and intervention groups (in-ICU). Severity of delirium: Difference in most severe ICDSC scores pre-post intervention between control and intervention groups (in-ICU). 3) Difference in the diagnosis of delirium in the medical chart, compared to usual care (when appropriate, i.e., when delirium is present) pre-post intervention between control and intervention groups (in-ICU). 4) Difference in mean CIDKQ scores pre-post intervention between control and intervention groups (in-ICU). 5) Difference in mean DEL-B scores pre-post intervention between control and intervention groups (in-hospital). The statistical significance of the differences between proportions or means (between the intervention and control groups) will be calculated using the.

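### Delirium days and delirium-free days are counted only in ICU and as a pre-post change, so a shorter stay can look like harm and the two measures can disagree

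*Protocol article*

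**What the plan says.** The Statistical analysis plan section gives two day counts under secondary aim 2. The first is duration: "Difference in mean days with clinical delirium (ICDSC score ≥ 4) pre-post intervention between control and intervention groups (in-ICU"). The second is its complement: "Duration of delirium-free days: Difference in mean days without delirium on the ICDSC pre-post intervention between control and intervention groups (in-ICU"). Both are confined to ICU and both are described as pre-post.

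The Secondary aims section defines duration differently, as "duration (total days of an ICDSC score ≥ 4"), with no pre-post element. It does not list delirium-free days.

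The Eligibility criteria section fixes the observation time on either side of enrolment. On entry: "Participants will be recruited at any point during their ICU admission". On the end: "participation will occur to a maximum of 5 days, or until ICU discharge or death". Table 1 requires "Richmond Agitation Sedation Scale score ≥ −3 (eligible for delirium assessment") and excludes a Glasgow Coma Scale score below 9, both as entry criteria.

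The article does not say whether the day counts stop at study day 5 or run to the end of the ICU stay.

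**The concern.** A count of good days that stops at ICU discharge rewards staying in ICU. A patient who recovers and leaves early has fewer days on which to be recorded as free of delirium. The duration count has the mirror problem with death: a patient who dies early has fewer days on which to be recorded as delirious.

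Neither event is remote on the document's own account. The Background links delirium to longer hospital stays, so an effective intervention might shorten stay. The Sample size calculation bases its 20% loss on mortality in the study ICUs. Multiple imputation does not help, because days after discharge or death lie outside an in-ICU count and are not missing from it.

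The pre-post form adds a second difficulty. The pre period is whatever ICU time preceded enrolment, and the post period has its own variable end. Subtracting raw day counts over unequal exposure does not give a clear change score.

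At stake is the reading of the delirium day counts. Delirium-free days could suggest harm while delirium days suggest benefit, from the same patients.

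**Working it through.** **The plan's own figure.** No effect size is given for either day count. The trial size rests on chart-reported delirium, 10% against 30%, with 90% power, two-sided alpha 0.05 and 20% loss:

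- (1.960 + 1.282)² × (0.1 × 0.9 + 0.3 × 0.7) / 0.2² = 10.51 × 0.30 / 0.04 = 78.8, so 79 per group.
- 79 / 0.8 = 98.75, so 99 per group and N = 198, as stated.

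The size therefore reproduces and does not depend on the day counts.

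**Direction, from the text alone.** In-ICU delirium-free days = ICU days − delirium days.

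- Patient A: 5 ICU days, 2 delirious: 5 − 2 = 3.
- Patient B: discharged alive after 3 ICU days, 1 delirious: 3 − 1 = 2.
- Patient C: dies on day 2 without delirium: 0 delirium days, the best possible duration score.

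B had less delirium and left sooner, yet scores worse than A. Over a fixed 5 days with days after live discharge credited, A scores 3 and B scores 4.

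**Size, on assumed inputs.** The documents give no length of stay or daily delirium rate. Assume that further ICU stay is geometric with mean 5 days in controls, that 40% of ICU days are delirious, and that the intervention multiplies mean stay by 0.8 (to 4 days). Deaths are left out. With a 5-day cap, mean counted ICU days are (1 − 0.8⁵)/0.2 = 3.36 in controls and (1 − 0.75⁵)/0.25 = 3.05 with intervention. Without a cap they are 5 and 4.

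| Scenario (intervention − control) | In-ICU delirium-free days | Delirium days |
|---|---|---|
| Rate stays 40%, capped | 0.6 × (3.05 − 3.36) = −0.19 | 0.4 × (3.05 − 3.36) = −0.12 |
| Rate stays 40%, uncapped | 0.6 × (4 − 5) = −0.60 | 0.4 × (4 − 5) = −0.40 |
| Rate falls to 30%, capped | 0.7 × 3.05 − 0.6 × 3.36 = +0.12 | 0.3 × 3.05 − 0.4 × 3.36 = −0.43 |
| Rate falls to 30%, uncapped | 0.7 × 4 − 0.6 × 5 = −0.20 | 0.3 × 4 − 0.4 × 5 = −0.80 |

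In three of the four rows one measure reads as harm and the other as benefit. A fixed 5-day count with days after live discharge credited equals 5 − delirium days. It gives +0.12 and +0.43 in the two capped rows, so here it cannot contradict the duration result.

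**Pre-post differencing.** Assume ICU days before enrolment are geometric with mean 3 (variance 6), 40% delirious, and independent of the post period.

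- Variance of pre-enrolment delirium-free days: 3 × 0.24 + 0.36 × 6 = 2.88.
- Capped: the post value has SD 1.32 and the difference has SD 2.15. Variance ratio (2.15/1.32)² = 2.7.
- Uncapped: SD 2.90 and 3.36. Variance ratio (3.36/2.90)² = 1.3.
- With no treatment effect, the simulated between-arm contrast in the change was 0.00 to 0.01 day, so there is no bias.

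Independence is the unfavourable case. Differencing stops costing precision once the pre-post correlation exceeds SD(pre)/(2 × SD(post)), with SD(pre) = √2.88 = 1.70. That is 1.70/2.64 = 0.64 capped and 1.70/5.80 = 0.29 uncapped. Adjusting for the baseline value as a covariate avoids having to know the correlation.

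**The case against.** The case on the other side removes several stronger readings.

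- **Enrolment timing drives or biases the contrast.** A reader might infer this from the varying pre period. Allocation is 1:1 and stratified by site, so time in ICU before enrolment is balanced in expectation. What remains is variance and chance imbalance.
- **Comatose days are counted as delirium-free.** Nothing in the article says so. RASS below −3 and a Glasgow Coma Scale score below 9 are excluded at entry, and a later day without a valid ICDSC need not count as free of delirium. The handling is unstated and may sit in a fuller plan. It is not shown to be wrong.
- **All of secondary aim 2 is unreadable.** The discharge arithmetic concerns day counts. It does not carry over to ever/never delirium or the worst ICDSC score, and delirium-free days is an added summary, not part of the stated aim.
- **Controls have no reference point for the post period.** Table 2 schedules ICDSC at baseline/randomization and then daily, which can serve both arms.
- **The sign will be wrong.** The stated hypothesis concerns duration and severity of delirium, not length of stay. With a 5-day cap and a lower daily delirium rate, the sign is right. For death to create a spurious difference between arms, deaths must differ between arms in number, timing or relation to delirium, and the documents do not suggest that.

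All of this stands. It does not remove the stated in-ICU restriction, the stated pre-post form, or the mismatch with the Secondary aims. Those are fixed in the text, so a fuller plan could mend them only by departing from it.

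**Conclusion.** The point holds for the two day counts. The direction of the discharge and death effects follows from the definitions without any assumption. The size does not: −0.19 day (5-day cap) to −0.60 day (no cap) rests on an assumed mean stay of 5 days, a 40% daily delirium rate and a stay shortened by a factor of 0.8. The result moves to +0.12 day capped, or −0.20 uncapped, if the daily rate also drops to 30%. The variance cost of differencing, 1.3- to 2.7-fold, assumes a mean of 3 ICU days before enrolment and no pre-post correlation, and would be smaller with positive correlation. The two definitions of duration conflict whatever the inputs. This is a secondary-outcome matter worth correcting; it does not touch the primary aim or the stated sample size.

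**What to change.** 1. Count from randomisation in both arms over one fixed window, for example the 5 study days.
2. Score days after live ICU discharge as delirium-free and days after death as not delirium-free. Report deaths beside delirium days, because this scoring does not by itself correct that count.
3. State how unassessable days (RASS below −3) are handled.
4. Replace pre-post differences with a comparison of post-randomisation values, adjusted for site, baseline ICDSC and ICU days before enrolment.
5. Reconcile the definition of duration in the Secondary aims with that in the Statistical analysis plan.

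The cost is mainly wording, since the ICU clinical information system already captures ICDSC, RASS and outcome data. The drawback is that delirium after ICU discharge is not measured, so crediting those days is an assumption to state and vary. In the capped example at an unchanged 40% rate, if a share q of post-discharge days were delirious, the fixed-window difference would be (0.4 − q) × (3.36 − 3.05): +0.12 at q = 0, +0.06 at q = 0.2 and zero at q = 0.4. A sensitivity analysis over such a range would show how far the result depends on it.

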### Statistical analysis plan

All data will be analyzed as intention to treat. Descriptive statistics will be used to summarize the patient and family characteristics. For all analyses, we will consider a two-tailed *p*-value < 0.05 to be statistically significant, and will adjust for multiple comparisons (Bonferroni correction) in the primary analysis where appropriate. For the secondary aims, we will not correct for multiple comparisons with statistical procedures, but rather consider them in our interpretation. Subgroup analyses and a priori *covariates* to be considered are: presence of mechanical ventilation, RASS score, delirium subtype, patient frailty status (based on Clinical Frailty Scale scores), patient age, patient sex, caregiver age, caregiver sex, and baseline levels of symptoms of depression, anxiety, and psychological distress. Linear regression models will be used to assess for effect modification and confounding. Missing data will be tabulated for all outcomes. If more than 5% of outcome data is missing, multiple imputation will be employed; for the primary aim, we will also conduct a sensitivity analysis assuming the data is missing not at random.

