#### Sample size calculation

*Primary Outcome:* To find a difference in the mean score on the PHQ-9 or GAD-7 of 3-points (from 13 to 10), with a standard deviation of 5-points, power of 90%, an alpha level of 0.05, and 20% loss to follow-up (based off of previous mortality rates in the study ICUs [local data]), 72 dyads per group are required (*N* = 144). *Secondary Outcomes:* To find a difference in the proportion of delirium events reported in the medical chart (most conservative estimate based on secondary outcomes selected) of 20% (from 10 to 30%) at 90% power, an alpha level of 0.05, and 20% loss to follow up, 99 dyads per group are required (*N* = 198). The primary outcome requires a smaller sample size, and thus the most conservative number based on a secondary outcome is employed here.

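### The trial is sized on one charted-delirium proportion per arm, but secondary aim 3 is worded as a pre-post difference between arms; read as a change contrast, its 90% power depends on a pre rate and a correlation that the plan does not give

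*Protocol article*

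**What the plan says.** The Sample size calculation section rests the trial's size on secondary aim 3, the "difference in the proportion of delirium events reported in the medical chart (most conservative estimate based on secondary outcomes selected"). The planning values are a difference "of 20% (from 10 to 30%) at 90% power", with alpha 0.05 and 20% loss, giving 99 dyads per group (N = 198). The primary outcome needs only 144, so aim 3 accounts for the other 54 dyads. No pre-intervention rate and no pre/post correlation is given.

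The Statistical analysis plan section describes the same outcome as "Difference in the diagnosis of delirium in the medical chart, compared to usual care (when appropriate, i.e., when delirium is present) pre-post intervention", and the sentence goes on to compare control with intervention in the ICU. The measures under aims 2, 4 and 5 carry the same pre-post wording, for example "Difference in mean DEL-B scores pre-post intervention between control and intervention groups (in-hospital"). The primary aim and aim 1 do not; they are written as between-group differences at stated time points.

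The a priori covariates include "baseline levels of symptoms of depression, anxiety, and psychological distress". Charted delirium before randomisation, baseline CIDKQ and baseline DEL-B are not on the list. The sentence on significance testing refers to differences in proportions or means between the two groups, but the name of the test is cut off in the text available.

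**The concern.** Two adjacent sections describe different estimators for the outcome that fixes the trial's size. The sizing treats charted delirium as one independent yes/no observation per patient. The analysis wording, read naturally, subtracts a pre-intervention value and compares the change between arms. The variance of that contrast includes the pre-intervention proportion and depends on the pre/post correlation; neither is in the calculation.

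Randomisation balances the pre value on average, so subtracting it adds noise without removing bias unless pre and post are well correlated. The Eligibility criteria section lets dyads enter at any point of the ICU stay, so the pre window may be short or long and a strong correlation cannot be presumed. The covariate list does not recover the loss, because it omits the baseline of this outcome.

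At stake is whether the printed 90% power belongs to the analysis described. A smaller loss of precision of the same kind applies to CIDKQ and DEL-B if they are analysed as change scores and the pre/post correlation is low.

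**Working it through.** **Inputs from the protocol.** 10% v 30%; 90% power; alpha 0.05; two-sided ("For all analyses, we will consider a two-tailed" threshold of 0.05); 1:1 allocation; 20% loss.

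**Inputs assumed.** Pre-intervention charted rate p0, equal in both arms: 0 to 20%. Pre/post correlation ρ, equal in both arms: 0 to 0.5.

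**Step 1: reproduce 99 per group.** z-values 1.960 and 1.282; (1.960 + 1.282)² = 10.51.

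- Unpooled: 10.51 × (0.10×0.90 + 0.30×0.70) / 0.20² = 10.51 × 0.30 / 0.04 = 78.8, so 79. Then 79 / 0.8 = 98.75, so 99.
- Pooled: 81.96, so 82. Then 82 × 1.2 = 98.4, so 99.
- Continuity-corrected (92 per arm, giving 115 or 111) and one-sided (67 per arm, giving 84 or 81) versions do not match.

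Both matching routes use one proportion per arm.

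**Step 2: variance of the change contrast.** For an arm with post rate p1, the change has variance

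p0(1−p0) + p1(1−p1) − 2ρ√[p0(1−p0) p1(1−p1)].

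With p0 = 10% and ρ = 0, the sum over arms is (0.09 + 0.09) + (0.09 + 0.21) = 0.48, against 0.30 in the sizing. For general ρ it is 0.48 − 2ρ(0.090 + 0.1375) = 0.48 − 0.455ρ.

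**Step 3: power at 79 evaluable per arm.** Power = Φ(0.20/SE − 1.96). With p0 = 10% and ρ = 0, SE = √(0.48/79) = 0.078 and power = 73%. With ρ = 0.2 it is 81%, with 0.3 it is 86%, and with 0.4 it is 90%. Break-even: 0.48 − 0.455ρ = 0.30, so ρ = 0.18/0.455 = 0.40. The largest possible correlation between a 10% and a 30% yes/no variable is 0.51, so 0.40 is not a weak requirement.

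**Step 4: range over the pre rate.**

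| Assumed pre rate | Summed variance, ρ = 0 | Power at 79 per arm, ρ = 0 | N for 90% power, ρ = 0, with 20% loss | ρ needed for 90% at 79 per arm |
|---|---|---|---|---|
| 0% | 0.300 | 90% | 198 | none |
| 2% | 0.339 | 86% | 226 | 0.18 |
| 5% | 0.395 | 81% | 260 | 0.29 |
| 10% | 0.480 | 73% | 318 | 0.40 |
| 20% | 0.620 | 62% | 408 | 0.53 |

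**Step 5: the alternative.** In simulation with a 10% pre rate and 79 per arm, the change analysis had about 73%, 81%, 87% and 96% power at ρ = 0, 0.2, 0.3 and 0.5. A comparison of post values adjusted for the pre value had about 90%, 91%, 93% and 97%. Adjustment costs almost nothing when the correlation is low and gains when it is high.

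All these figures take every evaluable dyad as contributing to aim 3.

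**The case against.** The strongest reply is that the plan never uses the words change score or difference of differences. The testing sentence speaks of between-group differences in proportions, which fits the formula used, and the test itself is unnamed. The Secondary aims section states aim 3 simply as an effect on diagnosis compared with usual care. The pre-post tag is also attached to total delirium days and the worst ICDSC score, where a change over unequal windows would be an odd quantity. And if aim 3 counts only patients with delirium present, a patient not delirious before enrolment has no pre value. The tag might be loose wording about timing.

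This stands in part: the change contrast is the natural reading, not a settled one. It does not remove the conflict. The tag is used systematically for aims 2 to 5 and not for the primary aim or aim 1, and for CIDKQ a true before-and-after pair is described under Timing of intervention. The testing sentence fits either reading.

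It is also fair that the pre rate and correlation come from outside the documents. A reader might infer that the trial is shown to be underpowered, or that 90% power can hold only with strong correlation. The documents do not support that: the required correlation is 0.18 at a 2% pre rate, and there is no loss at 0%.

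For aims 4 and 5 no power is printed, so nothing stated is contradicted. A change-score comparison there is valid, only usually less precise than ANCOVA.

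**Conclusion.** The mismatch between sizing and analysis wording is real, and the sections should be reconciled. Its size is conditional. If aim 3 is tested as a change contrast at 79 evaluable per arm, power at zero correlation runs from 90% (nothing charted before enrolment) through 86%, 81% and 73% to 62% (pre rates of 2%, 5%, 10% and 20%). The 10% case borrows the lower planning rate, the only usual-care-like figure in the protocol, and needs ρ of about 0.40 to restore 90%.

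Two further inferences should be avoided. The primary outcome is not affected: it needs 144 dyads and the trial recruits 198. Nor would correcting the contrast guarantee 90% power for aim 3. The restriction to patients with delirium is a separate threat. The Background says delirium occurs in more than half of ICU patients; assuming about 40 evaluable per arm, even the simple 10% v 30% comparison has only about 61% power.

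This is worth correcting before analysis, but it does not undermine the trial's main question.

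**What to change.** 1. **Aim 3.** In the Statistical analysis plan, replace the pre-post wording with a between-arm comparison of post-randomisation charted delirium. Report a risk difference adjusted for pre-randomisation charted delirium (yes/no), for example by logistic regression with standardisation. This matches the one-proportion-per-arm form of the sizing.
2. **Aims 4 and 5.** Compare post CIDKQ and post DEL-B between arms by ANCOVA with the time-0 score as covariate, instead of a change score. State which of the repeated measurements is the post value; DEL-B is collected daily.
3. **Covariates.** Add pre-randomisation charted delirium, baseline CIDKQ and baseline DEL-B to the a priori list.
4. **Power statement.** Do not claim that these changes secure 90% power for aim 3 while its analysis is limited to patients with delirium; state the denominator with the power.
5. **If the change contrast is kept**, restate the 90% as conditional on the pre rate and correlation, with a range such as the table above.

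The cost is wording in the protocol or analysis plan. No extra dyads are needed. Table 2 already schedules CIDKQ and DEL-B at baseline, and the pre-enrolment chart status is something the present pre-post wording already requires.
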